## Abstract

**Background:**

Salt intake of schoolchildren in the Australian state of Victoria is high. To protect future cardiovascular health, interventions that seek to reduce the amount of salt in children’s diets are required.

**Objective:**

We sought to develop and pilot test a Web-based program (Digital Education to Limit Salt Intake in the Home [DELISH]) that aims to reduce dietary salt intake among schoolchildren and to improve child and parent knowledge, attitudes, and behaviors related to salt intake. This paper presents the DELISH study protocol, along with pilot findings used to inform the development of the program.

**Methods:**

The DELISH program is a 5-week Web-based intervention that targets schoolchildren aged 7-10 years and their parents. This is a single-arm study with a pretest and posttest design. We will assess change in salt intake through analysis of 24-hour urinary sodium excretion. Children and parents will complete online surveys assessing knowledge, attitudes, and behaviors related to salt intake. We will assess feasibility of the program via process measures, which include metrics to describe intervention uptake (eg, number of children who complete Web-based sessions and of parents who view online newsletters) and evaluation surveys and interviews conducted with children, parents, and schoolteachers. The first 2 Web sessions developed for children were pilot tested in 19 children aged 8-12 years.

**Results:**

Findings from pilot testing indicated that most children (session 1: 18/19, 95%; and session 2: 19/19, 100%) enjoyed completing each session and liked the inclusion of comic strips and interactive games. Commonly reported areas of improvement related to sessions being text and content heavy. Based on these findings, we simplified sessions and developed 3 additional sessions for use in the DELISH program. The DELISH program was implemented during June-December 2016. We expect to have results from this study at the end of 2017.

**Conclusions:**

To our knowledge, this is the first Australian study to examine the effectiveness of a Web-based program to reduce salt intake among children in primary school. If shown to be acceptable and effective in lowering salt intake, the DELISH program could be tested using a more rigorous randomized controlled trial design.

## Introduction

In adults, excess salt intake is associated with high blood pressure [1], which is a major risk factor for cardiovascular disease [2]. It has been predicted that lowering population salt intake would substantially reduce morbidity, mortality, and public health care costs [3,4]. As part of the global action plan to reduce noncommunicable diseases, the World Health Organization has recommended a 30% reduction in global salt intake by 2025 [5].

As in adulthood, childhood dietary salt intake is positively associated with blood pressure [1,6]. Findings from a meta-analysis of 10 controlled salt-reduction trials found that a 42% reduction in salt intake predicted a significant reduction in both systolic (–1.17 mm Hg) and diastolic (–1.29 mm Hg) blood pressure [7]. Although the magnitude of the association between salt reduction and blood pressure in children is relatively modest, blood pressure follows a tracking pattern from childhood into adulthood [8]; therefore, the public health benefits of shifting the distribution of population blood pressure levels is important [9]. Additional consequences of excess salt intake during early life include increased risk of obesity [10,11] and the development of taste preferences for saltier foods [12,13].

The most recent (2011-2012) Australian national estimates of sodium intake, determined via 24-hour dietary recall, showed that average intakes were 2058 mg/day (salt equivalent 5.2 g/day) among 4- to 8-year-old children and 2462 mg/day (salt 6.3 g/day) among 9- to 13-year-old children [14]. This is in excess of dietary recommendations, which specify daily intakes of no more than 1400 mg/day (salt equivalent 3.5 g/day) and 2000 mg/day (salt 5 g/day) for each respective age group [15]. Using the reference standard measure of 24-hour urinary sodium excretion, we have previously reported an average salt intake of 6.1 g/day among 4- to 12-year-old schoolchildren in Victoria, Australia, with 72% of children exceeding the age-specific guideline for salt intake [16]. These findings demonstrate the need for strategies that seek to reduce salt intake among Australian schoolchildren.

Past evidence indicated that educational messages targeting the key sources of salt in the diet [17] and behavioral skills, such as reading food labels to select lower-salt foods [18] or using herbs and spices instead of salt to flavor food [19], are key components of effective programs to reduce salt intake in adults. However, there is little evidence of effective behavioral-based strategies for reducing salt intake in schoolchildren. The expansion of Internet technologies within the home in Australia [20] provides an important opportunity to deliver public health interventions. In 2014-2015, 97% of Australian households with children aged under 15 years had access to the Internet [20]. Although there is a social gradient for Internet access in Australia, access among more marginalized groups is still relatively common (eg, 77% of those educated to grade 12 or below have Internet access) [20]. Research suggests that online technologies can be used to engage children to achieve positive changes in dietary behaviors [21,22], for example, improved intakes of fruit and vegetables [23]. To date, no Web-based behavioral intervention targeting salt reduction in Australian schoolchildren has been trialed. Hence, we sought to develop and pilot test a Web-based salt-reduction program that targets primary school children and their parents. The primary objective of the program is to reduce salt intake among children by 20% and improve child and parent knowledge, attitudes, and behaviors related to salt intake. Secondary objectives relate to taste preferences in children; these include (1) assessing their salt preference for commercially available foods of varying salt concentration, (2) assessing the association between salt preference and salt intake, and (3) assessing whether participation in the program alters salt preference.

The purpose of this paper is to describe the Digital Education to Limit Salt Intake in the Home (DELISH) program and data collection methods that we will use in the study. In addition, we report on findings related to the development of the program, which includes pilot testing of educational materials among a sample of children aged 8-12 years.

## Methods

### Study Design and Participants

The DELISH program is a 5-week Web-based intervention that targets schoolchildren in years 2-4 of schooling (ages 7-10 years) and their parents. This is a single-arm study with a pretest and posttest design. The age range of participants is restricted to facilitate the design of appropriate intervention materials with respect to reading ability and comprehension. Children and parents are targeted, as research suggests that interventions that target the whole family, as opposed to only the parent or child, are more effective for achieving dietary changes [24]. Ethics approval has been granted by the Deakin University Health Human Ethics Advisory Group (Project No. HEAG-H 37/2016) and the Department of Education and Training, Victoria State Government (2015_002884). We will obtain written informed consent from the primary caregiver and assent from the child before their participation. This study is supported by a Heart Foundation Vanguard grant (Application ID: 100574).

### Recruitment Procedures

We will recruit children from government primary schools located in the Greater Geelong Region of Victoria, Australia. We will use a Web-based school locater search engine to identify schools with enrollments for primary school children [25]. The school’s postcode and corresponding Index of Relative Socio-economic Advantage and Disadvantage [26] will be used to group each school into low-, medium-, and high-socioeconomic areas of Victoria. Following this, we will randomly select schools from each tertile and invite each school’s principal to participate in the study via an email invitation and a follow-up courtesy call reminder. Classroom teachers will be provided with information about the study. Prior to school participation, written consent will be obtained from the school principal and classroom teachers. Following this, children in school grades 2-4 (7-10 years of age) will receive a study information pack, which will include an invitation letter addressed to parents, and a parental and child plain language brochure and consent forms. We will also advertise the study through the schools’ newsletters.

### Inclusion Criteria

Inclusion criteria are that children (1) will be required to have a parent with an email address and have access to a computer or tablet at home with an Internet connection, and (2) must be attending a Victorian government primary school in years (ie, grade) 2-4.

### Intervention Overview

The Web-based program will be delivered over a 5-week period. Children will actively participate in weekly Web-based sessions designed to take approximately 20-30 minutes each to complete. Parents will receive concurrent educational materials through weekly online newsletters sent via email and short message service (SMS) text messages. In addition, there will be a central study website, where resources for children and parents will be posted.

### Sample Size Calculations

We designed the intervention to reduce salt intake by 20% (ie, 1.2 g/day of salt). Using a random intercept multilevel model (with salt intake outcome allowed to vary randomly at both the individual and the school level) to estimate the change in salt intake over time (pre vs post as a fixed effect) and assuming a mean baseline salt intake of 6.0 (SD 2.5) g/day and intraclass coefficient of 0.04 (school clusters), we require a sample size of 102 children to detect a difference of 1.2 g/day of salt with 90% power at *P*<.05. Anticipating a 20% rate of dropout or incomplete urine samples returned, we aim to recruit 122 children across 6 schools.

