## Discussion

Lowering exposure to dietary salt during childhood is likely to have important cardiovascular health benefits [70]. In Australia, no Web-based behavioral programs to reduce salt intake among schoolchildren have been developed or tested. The process findings related to usability and acceptability of the DELISH program by parents and children, along with teachers’ views on incorporating salt-reduction messages within school nutrition programs, can be used to refine and modify the program as necessary. We acknowledge that the study is limited by the pretest and posttest design; as such, any reported changes in outcomes could be due to other confounding factors, such as wider health-related initiatives conducted at the participating schools. If shown to be acceptable and effective in lowering salt intake, the DELISH program could be tested using a more rigorous randomized controlled trial design.

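### The stated random-intercept model does not yield 102 children at 90% power: the school ICC cancels from the pre-post change, and the within-child correlation that drives the number is not given

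*Protocol article*

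**What the plan says.** The Sample Size Calculations section of the protocol article gives these elements:

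- Target: "We designed the intervention to reduce salt intake by 20% (ie, 1.2 g/day of salt".
- Variability: "assuming a mean baseline salt intake of 6.0 (SD 2.5) g/day".
- Model: a "random intercept multilevel model (with salt intake outcome allowed to vary randomly at both the individual and the school level", used "to estimate the change in salt intake over time (pre vs post as a fixed effect".
- Clustering and result: "intraclass coefficient of 0.04 (school clusters), we require a sample size of 102 children to detect a difference of 1.2 g/day", with 90% power at the 5% level.
- Recruitment: 122 children in 6 schools, so 102 analysed children would be 17 per school.

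The section gives no within-child correlation and no SD of change. The Data Analysis section says only that multilevel regression will be used for change in salt intake, with adjustment for covariates. It does not describe the random part of the model.

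**The concern.** The paragraph presents the school ICC as an input that helps fix the number of children. In a single-arm design where every child and every school is seen on both occasions, a school intercept shifts the before and after values equally and drops out of the difference. A child intercept does the same. The ICC therefore cannot inflate the number under the model named, and the quantity that sets the precision of the change is missing.

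Two things are at stake. The power statement for the primary outcome cannot be traced to its own model. A reader may also take the ICC as evidence that school clustering is covered, when a random-intercept model has no term for schools that differ in how much their pupils change.

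**Working it through.** **Inputs.** From Sample Size Calculations: difference d = 1.2, SD = 2.5, school ICC = 0.04, power 90%, alpha 0.05 (taken as two-sided, since the article does not say), 6 schools. The within-child correlation rho is my assumption and is varied.

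**Attempt to reproduce 102 from the stated model.** With complete pairs, the variance of the mean change is 2 × SD² × (1 − rho) / n. Here rho is the total within-child correlation, made up of the school share plus the child share, so it is at least 0.04 under the stated ICC.

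n = 2 × SD² × (1 − rho) × (1.960 + 1.2816)² / d²

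= 2 × 6.25 × 10.507 / 1.44 × (1 − rho) = 91.2 × (1 − rho)

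Power with 102 children is Φ(d/SE − 1.96), with SE = √(12.5 × (1 − rho) / 102).

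| rho (assumed) | n for 90% power | SE at n = 102 | Power at n = 102 |
|---|---|---|---|
| 0 | 92 | 0.350 | 92.9% |
| 0.04 | 88 | 0.343 | 93.8% |
| 0.2 | 73 | 0.313 | 96.9% |
| 0.3 | 64 | 0.293 | 98.4% |
| 0.5 | 46 | 0.248 | 99.8% |

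Solving 91.2 × (1 − rho) = 102 gives rho = −0.12, which this model cannot produce. The figure is not reproduced.

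**Check of the cancellation.** The generalised least squares SE of the pre/post effect was computed for 6 schools × 17 children × 2 occasions, holding the child and residual variances fixed. Raising the school-intercept variance from 0 to 10 left the SE at 0.2801. The ICC acts only by taking its share of the fixed total SD, which lowers n from 92 to 88.

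**What would give 102.**

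- A design effect on the change: 1 + (17 − 1) × 0.04 = 1.64. Then 91.2 × (1 − rho) × 1.64 = 102 gives rho = 0.318.
- A design effect of 102 / 91.2 = 1.12 with rho = 0, which is about 4 children per cluster at ICC 0.04.

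Both need a value that the article does not state, and the second does not fit 17 per school. The route actually taken is unknown.

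**If clustering of change was intended.** Take 102 children in 6 schools and rho = 0.318, and let the ICC of the change scores vary (assumed values). The design effect is 1 + 16 × ICC. The size of a nominal 5% test that ignores this clustering is 2 × (1 − Φ(1.96 / √design effect)). Power for an analysis that respects it comes from the noncentral t on 5 df, with SE = √(12.5 × 0.682 × design effect / 102).

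| ICC of change (assumed) | Design effect | Size of the test ignoring it | Power, t on 5 df |
|---|---|---|---|
| 0 | 1.00 | 5.0% | 91% |
| 0.01 | 1.16 | 6.9% | 86% |
| 0.02 | 1.32 | 8.8% | 82% |
| 0.04 | 1.64 | 12.6% | 74% |

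At rho = 0.5 and a change ICC of 0.04, power on 5 df is 85%.

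**The case against.** The strongest reply is that the discrepancy is on the safe side. The stated model needs at most 88 children at its own ICC, so 102 is more than enough, and what is shown is an opaque derivation. That stands.

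A reader might infer more: that the study is underpowered at about 74%, or that the primary test really runs at 12% to 13%. The article does not support either. Its ICC is attached to salt intake, not to change, and it gives no between-school variance of change. Those figures are one end of an assumed range. At rho 0.318, a change ICC of 0.04 means a school SD of change of √(0.04 × 12.5 × 0.682) = 0.58 g/day, nearly half the target effect.

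Nor does the Discussion supply the missing evidence. Its remark that "any reported changes in outcomes could be due to other confounding factors, such as wider health-related initiatives conducted at the participating schools" concerns confounding of the average change in an uncontrolled design. It does not say that change differs between schools, and a school-level random slope would not remove that bias.

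It is also fair that the random part of the analysis model is not fixed in Data Analysis and may be set out in a document not shown. An over-optimistic P value is therefore conditional. Finally, cancellation is exact only for complete pairs. If children with a single usable urine sample are kept, the intercept variances re-enter slightly.

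None of this makes 102 at 90% follow from the model stated. A condensed article may leave inputs out, but here the ICC it reports cannot do the work it appears to be given.

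**Conclusion.** The point holds as an error of derivation. For complete pairs, the stated random-intercept model needs 91.2 × (1 − rho) children, which is 88 or fewer at the stated ICC. With 102 children its power is about 94% to over 99% for rho from 0.04 to 0.5, not 90%. This rests on the article's own SD, difference, power and alpha, with alpha two-sided. The algebra is secure.

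The consequence for inference is conditional. If the analysis uses random intercepts only, and if change varies by school with an ICC of 0.01 to 0.04, the nominal 5% test would run at about 7% to 13%. With no such variation it would run at 5%.

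**What to change.** Restate the sample-size paragraph with the assumed within-child correlation or the SD of change, and say whether the 0.04 refers to intake or to change.

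- **If the random-intercept model is meant:** drop the inflation for the school ICC and report the power that 102 children give over a stated range of rho.
- **If clustering of change is meant:** say so, and quote power for a model that includes it over a range of change ICC, as in the second table. Add as a sensitivity analysis the mean of the 6 school-level changes with t on 5 df. With only 6 schools this suits a sensitivity analysis better than a replacement for the primary model, because it costs power even when schools do not differ (98.6% falls to 91% at rho 0.318).

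The cost is a reworded paragraph and one additional analysis, with a wider interval in that analysis. The article reports that data collection is finished and analysis still to come. Recruitment cannot change, but the description and the sensitivity analysis can.

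### Minor arithmetic error: the 20% loss allowance is applied by multiplying (102 × 1.2 ≈ 122) instead of dividing (102 / 0.8 ≈ 128), so 122 recruits give about 98 evaluable children in expectation, not 102

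*Protocol article*

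**What the plan says.** All the figures are in the protocol article, under Sample Size Calculations. The effect to be detected is a 20% reduction: "We designed the intervention to reduce salt intake by 20% (ie, 1.2 g/day of salt"). The planning inputs are given as "assuming a mean baseline salt intake of 6.0 (SD 2.5) g/day and intraclass coefficient of 0.04 (school clusters"), within a random-intercept multilevel model of pre versus post intake. From these the article concludes "we require a sample size of 102 children to detect a difference of 1.2 g/day of salt with 90% power". The next sentence makes the allowance for loss and sets the target: "Anticipating a 20% rate of dropout or incomplete urine samples returned, we aim to recruit 122 children across 6 schools".

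No other section gives a different loss rate, a rounding rule or another basis for 122. The Urine Collection section names change in the child's salt intake, from a 24-hour collection, as the primary outcome and lists the criteria for a complete sample. The section on data collection in the main study says that collection ended in December 2016.

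**The concern.** An anticipated rate of dropout or incomplete samples describes what happens to children who have been recruited, because only an enrolled child can drop out or return an incomplete collection. The recruitment target should therefore be the required number divided by the fraction expected to remain. Multiplying the required number by one plus the loss rate takes the 20% from the smaller number, and the result is too low.

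The sample size statement for the primary outcome is at stake. On its own loss assumption, the plan does not expect to end with the number that it ties to 90% power. The Discussion says that a randomized trial could follow, and the same inflation rule could be carried into that design.

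**Working it through.** **Inputs, all from Sample Size Calculations:** required number 102; power 90%; anticipated loss 20%; recruitment target 122; 6 schools; school intraclass coefficient 0.04. Significance level 0.05; sidedness is not stated, and two-sided is assumed here.

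**1. Reproduce the plan's target.** 102 × (1 + 0.20) = 122.4, which rounds to the stated 122. Rounding up, as is usual for a sample size, would give 123.

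**2. Target consistent with 20% loss among recruits.** 102 / (1 − 0.20) = 127.5, so 128. This is 6 more than 122. Check: 128 × 0.80 = 102.4.

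**3. What 122 delivers at 20% loss.** 122 × 0.80 = 97.6, about 98 children. The shortfall is 102 − 97.6 = 4.4.

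**4. Loss that 122 can absorb.** 1 − 102/122 = 20/122 = 16.4%.

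**5. Approximate power at 97.6 children.** Take 90% power at 102 as given and scale the standardized effect by the square root of the sample size:

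- z for two-sided 0.05 is 1.960 and z for 90% power is 1.2816; their sum is 3.2416.
- √(97.6/102) = 0.978.
- Power = Φ(3.2416 × 0.978 − 1.960) = Φ(1.211) = 0.887.

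If the clustering penalty also falls because the 6 schools contribute fewer children each, using 1 + (n/6 − 1) × 0.04:

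- Design effect at 102: 1 + 16 × 0.04 = 1.640.
- Design effect at 97.6: 1 + 15.27 × 0.04 = 1.611.
- Effective sizes: 102/1.640 = 62.2 and 97.6/1.611 = 60.6.
- Power = Φ(3.2416 × √(60.6/62.2) − 1.960) = 0.892.

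With 98 children in place of 97.6, the two versions give 0.888 and 0.893. The range is therefore 88.7% to 89.3%, or about 89%.

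**6. The same loss as a detectable difference.** At 90% power, by the simple scaling, 1.2 × √(102/97.6) = 1.23 g/day instead of 1.20 g/day.

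**What cannot be checked.** The 102 itself cannot be reproduced, because the within-child correlation between the pre and post measurements is not given. With a design effect of 1.64 (17 children per school), a two-sided paired calculation gives about 105 at an assumed correlation of 0.3, so a correlation slightly above 0.3 would give 102. None of steps 1 to 4 depends on this, since they take 102 as stated.

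**The case against.** The strongest counter-argument concerns consequence rather than arithmetic. About one point of power is small beside the uncertainty in the assumed SD and intraclass coefficient: the shift in detectable difference equals an error of about 0.06 g/day in the SD of 2.5 (2.5 × √(102/97.6) = 2.56). This stands, and it is why the point is minor.

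The target of 122 is an aim, and nothing in the recruitment procedures stops enrolment there. This also stands. A reader might infer that the study must end below 102 children. The documents do not support that: the 97.6 is an expectation, conditional on exactly 122 recruits and a 20% loss rate. Nor would 128 have secured 102. With independent losses at 20%, the chance of at least 102 evaluable children is about 19% with 122 recruits and about 59% with 128.

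The planned multilevel model could use a child with one valid collection, so some of the children counted as lost might still contribute partial information. That is possible, but the article does not say that they will be kept and does not use this to justify 122. It treats dropout and incomplete samples as losses to be made good. Counting them as contributing nothing is the plan's own accounting, and it may be pessimistic.

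Finally, 20% could be read as 20% of the 102 required. The wording describes a rate of dropout or incomplete return, which belongs to those recruited. Even on that reading, 122.4 would round up to 123.

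**Conclusion.** The recruitment target is wrong as written, and the error is minor. A requirement of 102, a 20% loss and a target of 122 are mutually inconsistent; the consistent target is 128. The size of the error is 6 recruits, about 4 evaluable children in expectation, and roughly one percentage point of power.

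The head counts rest only on the article's own 102, 20% and 122, with the loss rate applied to those recruited. The power figure also assumes a two-sided 5% test, that the stated 102 does give 90%, and that precision scales with sample size as shown; it should be quoted as approximate.

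A reader might go further and infer that the study is materially underpowered or that its results are in doubt. A fall from 90% to about 89% does not support that, and the precision achieved will depend on the number actually analysed. The inflation error is also no evidence that the 102 is wrong.

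**What to change.** Because data collection is complete, raising the target would serve no purpose. Keep 122 and correct the sentence on loss to say what it delivers: about 98 evaluable children and approximately 89% power at 20% loss on the stated assumptions, or 90% power only if loss is at most about 16%. Note that the target consistent with 20% loss would have been 128. If a randomized trial follows, its allowance should be computed by dividing by the retained fraction.

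The cost is one corrected sentence and a slightly less favourable power statement. No further children and no change to the analysis are needed.
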